## Abstract

**Background:**

Trigeminal neuralgia (TN) is a rare severe unilateral facial pain condition. Current guidelines in trigeminal neuralgia management recommend sodium channel blockers – carbamazepine or oxcarbazepine – as the first-line treatment. However, the currently available drugs are often associated with poor tolerability resulting in sub-optimal pain control. CNV1014802 is a novel sodium channel blocker that is being assessed in the treatment of trigeminal neuralgia. Due to the severity of the condition, it is not ethical to conduct a traditional placebo-controlled randomized controlled trial. It is also difficult to use an active control such as carbamazepine, the current gold standard, because of its complex pharmacology and potential for drug interactions.

**Methods/Design:**

The trial uses a randomized withdrawal design to assess efficacy in this rare condition. There is a 21-day open-label phase followed by a randomized 28-day placebo-controlled phase for responders. Thirty patients will be randomized. The primary outcome measure will be pain relief, but secondary measures of quality of life will be of significant importance given the effect of this condition on activities of daily living. Safety and adverse event endpoints are described.

**Discussion:**

There have been very few well-controlled, randomized, placebo-controlled studies in trigeminal neuralgia, and the majority of drugs have had other primary uses. Due to the severity of the pain, minimizing the time a patient is administered placebo was a key factor in designing this study. This study will not only provide data on the efficacy of CNV1014802 in trigeminal neuralgia, but will also provide information on the effectiveness and acceptability of a novel trial design in trigeminal neuralgia.

**Trial registration:**

Trial number NCT01540630

## Background

Trigeminal neuralgia (TN) is an uncommon episodic severe facial pain condition with an incidence of 4.0 to 4.7 per 100,000 persons per year [1,2]. Trigeminal neuralgia can appear at any age, but disease onset is over 40 years of age in over 90% of cases with peak onset between 50 and 70 years of age [2,3]. However, recent data from primary care practice data validated by experts suggest an incidence rate of 12.6 per 100,000 person years with a mean age at diagnosis of 51.5 (SD 17.6) with a female predominance 71% [4]. The classification system of the International Headache Association aims at establishing TN diagnostic criteria based on etiology [5]. Yet, there is a problem in distinguishing primary and secondary TN, because unless a patient with normal neuroimaging comes to an operation, it remains unclear if his/her TN is caused by a vascular compression. To adjust for this diagnostic uncertainty, the term “classical” neuralgia is currently used for cases with normal neuroimaging and potential compression of the proximal trigeminal nerve root by a vascular loop. Classical TN is the most common TN type, and it is thought that secondary demyelination, probably mediated by microvascular ischemic damage, results in a lowered excitability threshold of affected neurons. This promotes inappropriate ectopic generation of spontaneous nerve impulses together with abnormal nonsynaptic ephatic transmission to adjacent neurons [6,7].

Unlike many other neuropathic pains, TN results in recurrent paroxysms of short-lasting but very severe pain in the distribution of one or more branches of the trigeminal nerve. In patients with the classical type, the attacks come on suddenly, last up to 2 min and disappear suddenly. Between attacks, patients are usually asymptomatic, although there may be a slight after pain [8]. Numerous attacks occur a day, but currently there are no studies detailing how many paroxysms occur a day. In a recent RCT of botulinum toxin A in 42 TN patients, the frequency of paroxysms was measured, and the average was 20 a day, but the range was 4–100 [9]. Patients also report that these can be so frequent that it seems like one long attack. The attacks can vary in severity and be described as shooting, electric shocks scoring maximum scores on scales or just “twinges.” These attacks can then go on for weeks or months. Especially in the early stages of the disorder, it is very common for the attacks to stop completely and for patients to have weeks, months or even years of no pain [10]. However, over time the remission periods get shorter. Currently, there are no natural history studies or known prognostic factors to help determine how long these periods can be, although Taylor et al. [11] showed that carbamazepine became less effective with time. This may be due to the natural course of the disease, but may also be vested in the autoinduction pharmacological properties of carbamazepine itself. Pain is provoked by light touch activities, e.g., washing, eating, talking and cold winds, but spontaneous attacks of pain also occur. One study that measured the occurrence of evoked or spontaneous pain suggested that oxcarbazepine was more effective at reducing the former [12]. Although attacks of pain occur at night, these are less common. Thus, even when pain free, patients live in fear of pain return. These features therefore make it difficult to evaluate the effect of treatments. The diagnostic criteria for TN most frequently used are those of the International Headache Society, the International Classification of Headache Disorders (ICHD) [13], and these have now been updated with clearer specification of the variants of TN, i.e., those patients who may have in addition to the shooting stabbing pain a more prolonged pain, and these are thought to have a potentially different pathophysiology [14].

Current guidelines in trigeminal neuralgia management recommend sodium channel blockers such as carbamazepine or oxcarbazepine as the first-line treatment for pain control. However, these agents are often poorly tolerated [15] and often require lengthy dose escalation, resulting in sub-optimal efficacy, and some result in significant drug interactions and require careful monitoring. Other potential second-line therapies include lamotrigine, pregabalin, gabapentin and baclofen; there is limited evidence to support the use of these agents [15,16]. Unlike other medications used in chronic pain, these drugs often result in complete pain relief, not just 50%, especially in the earlier stages of the disorder.

All the drugs used to date have been initially developed for other uses, principally epilepsy, so dosage scales have had to be adapted. A review of RCTs and Cochrane systematic reviews (SR) shows that the major side effects reported from antiepileptic drugs (AED) were drowsiness from 100–4%, dizziness or vertigo 47–3%, gastrointestinal (GI) 57 to- 8%, mood changes 2%, dry mouth or taste change 4–2%, and headaches 4%. The SR on carbamazepine (CBZ) [17] reported 40–60% would have side effects. However, no study provides details on how these events were measured or quantified. Studies in healthy volunteers do show that AED drugs, especially the older ones such as CBZ, do result in cognitive impairment, although this is generally modest but can have clinical significance [18]. Memory, especially those tasks with an attentional component, is reduced when on CBZ [19,20]. However, it also needs to be noted that pain has an impact on cognitive function [21].

Thus, a well-tolerated sodium channel blocker that can be administered at an effective dose with no titration and good tolerability may address some of the unmet needs of this patient group.

CNV1014802 is a peripherally and centrally acting agent that inhibits sodium channels in a state-dependent fashion. CNV1014802 shows selectivity for the Nav1.7 subtype over the other subtypes tested (Nav1.1, Nav1.2, Nav1.3, Nav1.5, Nav1.6 and TTX-R), for both the resting and depolarized states. The greater block of Nav1.7 is particularly enhanced at concentrations below 1 μM, where the free exposure in animal models and human clinical doses lies.

In addition, the amount of block by CNV1014802 increases significantly and in a similar way with the frequency of stimulation for Nav1.7, Nav1.2 and Nav1.6. Combining all aspects of the pharmacology of CNV101802 at sodium channels, the block is more activity-driven at Nav1.2 and Nav1.6 than it is at Nav1.7, where it is substantial even at lower levels of activity of the channel. The block at Nav1.5 and TTX-R is significantly weaker.

Consistent with its mechanism of action, CNV1014802 will preferentially target and inhibit higher frequencies of firing (from 10 Hz onwards) that are attained following noxious stimuli or occur in chronic pain conditions or during seizure activity.

CNV1014802 has also been shown to selectively and reversibly inhibit the monoamine oxidase (MAO)-B enzyme, with no effect on MAO-A. One hundred percent inhibition of MAO-B was achieved with doses of 75 mg and above in the clinic studies.

A genetic substrate for neuropathic pain is an accepted hypothesis in the scientific community. Recently, sodium channel gene mutations causing cell hyperexcitability have been identified in groups of patients with painful neuropathy [22,23]. Calcium channelopathies have also been linked to migraine and epilepsy [24]. Given the importance of sodium and calcium channels in the generation, propagation and plasticity of pain signals, it is proposed to genotype five sodium channel (Nav1.1, Nav1.2, Nav1.3, Nav1.6 and Nav1.7) and two calcium channel (Cav2.2 and Cav2.1) genes in all patients entering the study to explore whether mutations in these genes are present in TN and whether these are related to response to treatment with CNV1014802.

CNV1014802 has completed extensive phase I studies with single and repeated doses in 166 healthy volunteers.

Moore et al. [25] in their analysis of analgesic drugs propose that high failure rates of drugs must be expected especially in chronic pain, that a radical re-think is necessary in the design of analgesic trials and that an enhancement enriched randomized withdrawal design may be the way forward, but currently they are poorly understood in part because few have been carried out.

Thus, the aim of this study is to design and test a protocol to evaluate the efficacy of a new sodium channel blocker, CNV1014802, in TN, which takes into account the difficulties encountered in previous trials in this area. An additional aim, if study participants agree, is genotyping for possible sodium and calcium channelopathies. The protocol was designed and approved prior to the SPIRIT 2013 statement, but will try to adhere to the published check list [26].

## Methods and design

A review of the literature was first carried out and showed that clinical trials in TN are challenging, and many of the published trials in this disorder have recruited low numbers of patients and have used variable designs and outcome measures, resulting in inconclusive outcomes [17,27-29]. Traditional placebo-controlled studies (crossover or parallel group) are difficult to run in this condition, as significant numbers of patients will be exposed to placebo for an extended duration. Using active controls is difficult as the gold standard drug carbamazepine is metabolized through the liver and so takes time to be eliminated and for the liver enzymes to return to normal function, thus necessitating extended washout periods. Because of the severe nature of the pain, patients are unlikely to accept extended periods of no treatment or use of placebos. Two-stage enhancement enriched randomized withdrawal designs (EERW) have recently been proposed as an alternative strategy for determining the effectiveness of analgesic drugs [30,31]. Although bias will occur as only responders are enrolled into the randomized part of the trial and they may also guess whether they are on the active drug or not, it does offer the patients a rapid termination and return to previous medication. Response to the open label part of the study also allows any adjustments to be made to the dosage and to evaluate whether the drug has any potential in the individual patient. A recent study using levetiracetam for TN showed poor efficacy in the open label phase, so the randomized trial was not started [32]. With a disorder that results in unexpected remission periods, it is essential to ensure that at the end of the trial it is established that the disease has not gone into remission.

Outcome measures were chosen according to the recently published recommendations from the International Association for the Study of Pain committee [33], which suggest the following areas should be assessed using psychometrically tested tools: pain intensity, physical and emotional functioning, participants global improvement and satisfaction, symptoms and adverse events, and participants disposition. Trigeminal neuralgia is unusual in that it is considered a chronic pain, but the pain is very clearly episodic. Attacks can vary in number and anecdotally patients have reported that a significant outcome is to have a reduction in pain attacks even if their intensity remains high. In an RCT of use of lamotrigine in TN, a composite score was obtained that included the number of bursts of pain, i.e., not individual stabs of pain but paroxysms of pain (none, 1–3, 4–7, 8–12, 13–20, over 20), severity of pain (no pain, mild, moderate, severe) and degree of pain relief (complete, good, moderate, slight, none) [34]. Thus, the number of paroxysms daily would also be used as an outcome measure, although there are no data on the number of attacks expected, but a 50% reduction would be considered successful. The pain intensity of each paroxysm is assessed on an 11-point numerical rating scale (PI-NRS). The Brief Pain Inventory-Facial (BPI-Facial), which is a validated 18-item rating scale for facial pain in a TN population [35], is also included as a composite assessment of efficacy, which includes the impact of pain on quality of life.

Special emphasis will be placed on adverse events as drugs such as carbamazepine are highly effective, but their tolerability is very poor, thus limiting their use. A scale that has been developed and tested in large numbers of patients with epilepsy is the adverse events profile (AEP) by Baker et al. [36,37]. This would provide more quantifiable data than have previously been reported.

Although measuring cognitive function is complex and it has been suggested that self-administered scales may have a much stronger relationship to participants’ mood rather than their objectively measured cognitive performance, some attempt will be made to measure this using the Medical Outcomes Study-Cognitive Scale (MOS-Cog) [38,39].

Genotyping is not mandatory for patients participating in the study.

The trial was designed by the chief investigator (JZ) and the Convergence team with protocol review by two outside neurologists with experience in this disorder and later by two of the authors ([name]) Additional file 1. A brief summary of the trial was presented at a UK Trigeminal Neuralgia support group meeting to determine whether patients would take part in the study and whether the correct outcome measures were chosen. Expert patients were asked to comment on the patient information sheet, consent form and diary card. The study has been approved by regulatory authorities and ethics committees in 11 countries: the UK, Germany, Switzerland, Estonia, France, Italy, Latvia, Lithuania, Romania, South Africa and Spain. The names of the committees are to be found in the Additional file 2, Ethics Committees. Although it is anticipated that patients will be referred in from the community, the study will take place in secondary care centers, which have a special interest in headache and facial pain.

The trial was designed to use an initial dose of 150 mg three times daily with the flexibility to use a higher dose regimen of 350 mg twice daily if appropriate. A review of efficacy data after the first ten patients had completed the open label study was planned to review efficacy and tolerability. If these were acceptable, as judged by a data monitoring committee, then the trial would continue to completion without changing the dose. All investigators and their teams met for 1 day to undertake training and review the protocol, and the operational practicalities of the study including site selection, monitoring and data management were taken over by a contract research organization (CRO).

The outline protocol is available at http://www.clintrials.gov, trial no. NCT01540630, and gained ethical approval in the UK in September 2011, then subsequently in all the other participating countries. A final harmonized version of the protocol, incorporating all country-specific minor amendments, was available in August 2013.

A double-blind, randomized withdrawal study comparing CNV1014802 with placebo in patients with TN who have successfully responded to CNV1014802 in an initial open-label phase was designed to take into account all the difficulties highlighted in the Methods section. Figure 1 shows the overall design of the study.

**Figure 1 F1:**
[figure not shown]
Design of the study.

### Design

Patients participate in an initial open-label treatment period of 21 days of CNV1014802 using 150 mg three times daily. Responders are then randomized to 28 days of CNV1014802 150 mg three times daily or placebo.

A responder at the end of the open-label period was defined as a patient with one of the following:

• A 30% or more decrease in the total number of paroxysms over the last 7 days of the open-label phase as compared to the total number recorded in the 7-day baseline phase (day -7 to -1 prior to start of study medication)

• A 30% reduction in the mean severity of pain experienced during the paroxysm over the last 7 days of the open-label phase as compared to the total number recorded in the 7-day baseline phase (day -7 to -1 prior to start of study medication)

• A Patient Global Improvement of Change rating of much improved/very much improved

### Randomization and allocation concealment mechanism

In the initial open-label treatment period, all patients will receive CNV1014802.

Patients will be randomized to CNV1014802 or placebo, in a 1:1 ratio, in accordance with the randomization schedule. The randomization schedule will be generated by the CRO using the PROC PLAN procedure of SAS®, a validated computer system. Eligible patients will be randomized into the study on day 21. The randomization schedule will be stratified by whether the patient is on existing pain medication (adjunct) or not (monotherapy). Equal numbers of patient on adjunct and monotherapy are not required.

### Outcome measures

The primary outcome measure of efficacy is the number of treatment failures on CNV1014802 vs. number of treatment failures on placebo throughout the double-blind treatment period. Patients are classified as a treatment failure if they meet one of the following criteria:

i. A 50% increase in the frequency of paroxysms compared to the final 7 days of the open-label period to more than three paroxysms within a 7-day period

ii. When more than three paroxysms are reported in a 7-day period, a 50% increase in the severity of pain experienced in the paroxysms compared to the final 7 days of the open-label period

iii. A Patient Global Improvement of Change rating of much worse/very much worse

iv. The patient discontinues the study because of ‘lack of efficacy.’

v. The patient discontinues because of an adverse reaction or poor tolerability considered to be related to the study medication

During the double-blind randomized phase, patients will be evaluated to determine whether they meet the failure criteria at each clinic visit, which will occur every 7 days in the double-blind treatment period. The data for the frequency and severity of the pain will be taken from the daily diaries completed by the patients. Figure 2 is an example of such a diary.

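### Failure criterion ii cannot be met from a final open-label mean severity above 6.67 (0–10 scale assumed), so some full severity relapses can count only through the other failure criteria

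*Protocol article*

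**What the plan says.** **The failure rule.** Under Outcome measures, meeting any one listed criterion makes a patient a treatment failure. Criterion ii is the only one built on diary severity. It applies "When more than three paroxysms are reported in a 7-day period" and then requires "a 50% increase in the severity of pain experienced in the paroxysms compared to the final 7 days of the open-label period". The article gives no alternative in terms of an absolute rise or a return to the pre-treatment level.

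**The scale.** Under Methods and design: "The pain intensity of each paroxysm is assessed on an 11-point numerical rating scale (PI-NRS"). The end points of the scale are not printed.

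**Who is randomized.** Under Design: "A responder at the end of the open-label period was defined as a patient with one of the following". The three routes are:
- frequency: "A 30% or more decrease in the total number of paroxysms over the last 7 days of the open-label phase"
- severity: "A 30% reduction in the mean severity of pain experienced during the paroxysm over the last 7 days of the open-label phase"
- global rating: "A Patient Global Improvement of Change rating of much improved/very much improved"

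Only the second route involves severity, and no route sets an upper limit on it. Entry to the open-label phase requires attacks rated 4 or more, again with no upper limit.

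**Expected severity.** The Background says: "The attacks can vary in severity and be described as shooting, electric shocks scoring maximum scores on scales"; the same sentence goes on to mention very mild attacks. Methods and design adds that patients value having fewer attacks even when each one stays intense.

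**The concern.** A relative rise on a bounded scale runs out of room at the top. A patient whose attacks became fewer but stayed intense can enter the double-blind phase at a level from which criterion ii cannot be reached, however bad the pain becomes. If that patient had gained something on severity and loses it on placebo, the endpoint's severity component does not register the loss. The other criteria may register it, but none of them measures severity from the diary. Placebo failures missed in this way would narrow the contrast that the trial is sized on, 20% against 67%.

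**Working it through.** **Inputs.** From the article: the 50% failure threshold, the 30% response threshold, the 11-point scale, and failure rates of 20% and 67% with 11 evaluable patients per arm and a one-sided 5% test (Power calculation). Assumptions: the scale runs 0–10; criterion ii is applied to weekly means; the severity response is measured against the baseline mean severity (the printed comparator repeats the wording of the frequency rule).

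**1. The plan's own figure.** The article gives no figure for the scale limit. Its sample size does reproduce, with the unpooled normal approximation:

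n = (1.645 + 0.842)² × (0.20×0.80 + 0.67×0.33) / 0.47² = 10.67, so 11 per arm, with power 81.1%.

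That figure is not in dispute here.

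**2. The ceiling.** Severity needed = 1.5 × open-label mean.

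| Open-label mean | Needed for criterion ii | Reachable on 0–10? |
|---|---|---|
| 4 | 6.0 | yes |
| 5 | 7.5 | yes |
| 6 | 9.0 | yes |
| 10/1.5 = 6.67 | 10.0 | only at the maximum |
| 7 | 10.5 | no |
| 8 | 12.0 | no |
| 9 | 13.5 | no |

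If the 11 points ran 1–11, the limit would be 11/1.5 = 7.33.

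**3. Full loss of a gain.** After a fractional fall f, a complete return to baseline is a rise of 1/(1−f) − 1.
- f = 25% (10 to 7.5 and back): +33.3%
- f = 30% (10 to 7 and back, or 6 to 4.2 and back): +42.9%
- f = one third: +50%

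So a full return reaches 50% only after a fall of at least one third. This holds at any baseline and is separate from the ceiling. Below the ceiling, a rise beyond baseline can still count: from 4.2 the patient needs 6.3. Above 6.67, even the scale maximum does not count.

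**4. Severity responders at the ceiling.** A 30% fall leaves the mean above 6.67 when baseline exceeds 6.67/0.7 = 9.52. Patients who just meet the response from there enter at 6.67 to 7.0.

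**5. How many?** The article gives no severity distribution. For illustration, take baseline means as normal with SD 1.5, truncated to 4–10, and the same proportional fall in every patient. The share who could not meet criterion ii is then:

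| Open-label fall | Baseline mean 6 | 7 | 8 |
|---|---|---|---|
| 10% | 19% | 39% | 62% |
| 20% | 6% | 17% | 35% |

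The spread from 6% to 62% shows that the assumption drives the answer. These are shares for whom criterion ii is unavailable, not shares of missed failures.

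**6. Sensitivity of power.** With the formula of step 1 at 11 per arm, assumed losses of 5%, 10% and 20% of placebo failures lower the placebo rate to 0.67×0.95 = 63.7%, 0.67×0.90 = 60.3% and 0.67×0.80 = 53.6%. Power becomes about 75%, 68% and 54%. Nothing in the article says what the loss would be.

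**The case against.** The strongest reply is that criterion ii is one route among several. A worsening patient can still fail through a 50% rise in frequency, a rating of much or very much worse, discontinuation for lack of efficacy, or need for a trigeminal neuralgia drug other than paracetamol. That stands. A reader might infer that severity relapses in patients randomized on frequency or global rating can never be counted. The article does not support this: those at or below 6.67 can meet criterion ii, and those above it have the other routes.

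Second, a patient whose severity never fell has no severity gain to lose. The same illustrative distribution with unchanged severity would put 36%, 59% and 80% of patients above the limit for baseline means of 6, 7 and 8. A reader might take these as missed relapses, which they are not. The benefit in such patients lay in frequency or global state, and criteria i and iii address those.

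Third, the distribution is assumed. Even the lower bound of 4 is not secure, because entry requires attacks of that intensity on only 4 of 7 days, so a weekly mean over all attacks could be lower. This stands as well, and it is why no share is claimed.

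Fourth, the 10-to-7-to-10 case is not purely a ceiling effect, since +42.9% falls short of 50% at any baseline. This is correct. It points to a related mismatch between the response and failure thresholds.

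What the reply does not remove is that the only diary-based severity criterion is inoperative for some patients whom the responder rule admits, including patients with a real severity gain to lose.

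**Conclusion.** The point holds in limited form. On a 0–10 scale, criterion ii cannot operate above a final open-label mean of 6.67, and the responder definition lets such patients be randomized. The patients who matter are those with a partial severity improvement that still leaves them above 6.67, who then relapse on severity without meeting any other criterion. Separately, a bare 30% severity response that is fully lost does not meet the 50% failure threshold at any baseline.

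The size of the group and the effect on power cannot be derived from the article. A reader might conclude that the planned 80% power is lost. That does not follow, because the 67% placebo rate is given without derivation and nothing shows that it ignores the limits of the definition. Missed placebo failures would reduce the observed difference; they would not create a false positive. This is a definitional weakness in the primary endpoint, cheap to correct and worth correcting before unblinding, but it does not invalidate the trial. The conclusion rests on the 0–10 reading of the scale; a 1–11 reading moves the limit to 7.33 and changes nothing else of substance.

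**What to change.** For scoring of the primary endpoint only, keep criterion ii and add:

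*Where 1.5 times the open-label mean severity exceeds the scale maximum, and the day −7 to −1 mean was higher than the open-label mean, criterion ii is met by a return to at least the day −7 to −1 mean, provided the rise from the open-label mean reaches a pre-specified minimum (for example 1 point).*

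The 10-to-7.5-to-10 patient, with a rise of 2.5 points, would then be counted. The minimum rise is needed: without it, an open-label mean of 6.8 with a baseline of 6.9 would fail on a rise of 0.1 point, which is diary noise.

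The plan should also:
- print the scale's end points;
- reconcile the 30% response and 50% failure thresholds, or state that a fully lost 30% response is deliberately not a failure (the added sentence does not reach patients at or below 6.67);
- state that patients with no severity improvement and a mean above 6.67 can be assessed only by the other criteria.

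The cost is one sentence in the definition and a change to the failure derivation, using diary data already collected. The downsides are a few more failures scored in either arm, and a remaining step at the limit: an open-label mean of 6.6 needs 9.9, a rise of 3.3 points, while one just above 6.67 may need much less.
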